#### Criteria for discontinuing or modifying allocated interventions {11b}

Participants reporting neck pain would be examined during a clinical visit to assess whether the exercises are being performed as described in the protocol. If the participant develops severe neck pain (sudden severe sustained lasting 24 h) that does not resolve within 48 h, the participant would be referred to their treating physician for follow-up care. Medication will be prescribed for symptomatic relief as deemed appropriate by the participant’s treating physician. If the severe neck pain persists 3 days after treatment, the intervention would be discontinued. Modifications to interventions or discontinuation of study interventions will be documented on a protocol deviation form.

#### Strategies to improve adherence to interventions {11c}

In addition to the exercise program, we will provide a weekly paper exercise completion grid for participants to record exercise completion. The exercise completion grid will also serve as a reminder to complete the exercises. We will also use the information provided in the exercise grid to track compliance. We will provide the participant with a new exercise grid at each visit. We have used this method with success to assist the completion of weekly exercises and track compliance in prior studies [19].

#### Relevant concomitant care permitted or prohibited during the trial {11d}

There are no prohibited interventions, although we will request that participants not enroll in any other clinical trial comparing balance therapies for the duration of their INVENT VPT participation.

#### Provisions for post-trial care {30}

Medical care will be provided to participants that may experience harm from participating in the INVENT VPT Trial. The cost for any treatment or hospital care that may be received because of a study-related injury will be billed to the participant if not covered by a health insurer. The participant does not waive their rights to seek compensation for any injuries received because of trial participation.

### Outcomes {12}

The primary outcome measure will be VOR gain (eye velocity/head velocity) as measured using the video-head impulse test (vHIT). The vHIT affords us the ability to identify other mechanisms of gaze stability (i.e., compensatory saccade); thus, we will also capture metrics related to compensatory saccade frequency and latency. We will assess inter-trial correlations for both VOR gain and compensatory saccade latency. Secondary outcome measures include compensatory saccade metrics and those that capture data in the participative and impairment domains. Participative domain measures include the Dizziness Handicap Inventory (DHI), the Activities-Specific Balance Confidence Scale (ABC), the Neurobehavioral Symptom Inventory (NSI), and the Patient Global Impression of Change (PGIC). Finally, a one-time characterization of hearing and vestibular function will be obtained at enrollment.

#### Participative measures

The DHI measures a participant’s perception of how the dizziness impacts their life. The index considers the emotional, physical, and functional aspects of their quality of life. Clinical significance is defined as a decrease in the DHI of either 18 points or 42% from the pre-treatment level [19]. VPT is known to reduce DHI score [20–22].

The ABC is a self-reported instrument that asks participants to rate their confidence performing 16 activities of daily living [23, 24]. Scores range from 0 indicating no confidence to 100 indicating complete confidence in the participant’s ability to perform the task without losing their balance. Scores < 67% indicate a risk for falling and accurately classify people who fall 84% of the time [25]. The ABC has excellent test-retest reliability (*r* = 0.92), and VPT is known to improve the ABC score [26].

The NSI collects data on the symptoms experienced after an mTBI. We will follow the Department of Defense’s suggestion that an individual experiencing a minimum of 20% score improvement from baseline is considered significant [27].

The PGIC is a commonly used method to quantify the amount of improvement the patient believes has occurred since beginning treatment (i.e., intervention). The PGIC asks one question that is rated on a 7-point Likert scale. PGIC values of 6 or more correlate best with actual change [28].

#### Impairment measures

Impairment domain measures include the dynamic visual acuity test (DVA), the instrumented stand and walk test (ISAW), vertical and torsional alignment nulling (VAN and TAN), and the following clinical measures that we will instrument using inertial measurement units (9 degrees of freedom sensors)
Functional gait assessment (FGA)Gait speedTandem walkModified clinical test for sensory integration of balance (mCTSIB)

The DVA test will measure visual acuity during active impulse head rotations. Participants will wear a headband with a rate sensor attached that triggers a flashing letter once head velocity crosses a predetermined threshold. Participants will generate a single head rotation to the right and left (impulses, separately) with performance being assessed from the size of the smallest letter the participant can identify [19].

The ISAW uses wireless sensors to measure a 30-s stand, 7-m walk, followed by a 180° turn. ISAW can distinguish soldiers with mTBI from healthy controls by their longer duration to turn (*p* < 0.001), their increased number of steps to complete a turn (*p* < 0.001), and their decreased peak velocities during the turn (*p* = 0.003) [28].

During vertical alignment nulling and torsional alignment nulling (VAN, TAN), the participant views one red and one blue line on the tablet screen through color-matched red and blue filters. The tests measure the perception of ocular alignment and are reliable and valid in conditions of otolith dysfunction.

The FGA is an 8-item scale that was developed to determine fall risk in older adults. Participants are scored on a 4-level ordinal score while they perform various ambulation tasks. Scores < 20 indicate an increased risk of falling in older adults.

The Patrol Exertion Multitask Test (PEMT) involves significant cognitive demands of situational awareness, memory, and decision-making under the physical stress of moderate exertion. The PEMT is a 12-min test where participants view a virtual patrolling scenario while responding to intermittent and unpredictable reaction timing cues. During this, they report visual clarity and perceived exertion. The PEMT has excellent interrater reliability for the assessment of cognitive (ICC 0.97), visual (ICC 0.99), and exertional (ICC 0.98) domains and can distinguish active-duty service members (SM) with mTBI from healthy control service members based on scores of visual clarity and reaction time [29].

The Modified Clinical Test of Sensory Interaction on Balance (mCTSIB) tasks participants to stand quietly (arms folded) while sway and time are measured under four conditions: (1) eyes open firm surface, (2) eyes closed firm surface, (3) eyes open unstable surface (foam), and (4) eyes closed unstable surface (foam). The best possible timed scores are 30 s for each item or 120 s total score.

### Participant timeline {13}

Table 1 illustrates the enrollment, interventions, and assessments of the INVENT VPT Trial. The primary outcome is VOR gain as measured by the vHIT. Secondary outcomes include participative and impairment measures. During the enrollment/baseline visit, participants will receive an initial VOR characterization and complete assessments for determining exercise treatment intensity. Participants will be randomized to IVE washout period-VPT or VPT-washout period-IVE. The washout period varies as do the timing of follow-up assessments by aim.

### Sample size {14}

We have based our estimate of sample size on data published in healthy adults (21–58 years old) using the IVE paradigm, whose age reflects our target patient population [30]. In that study, active VOR gain pre-adaptation was 0.92 ± 0.18 and active VOR gain post adaptation was 1.11 ± 0.22. Therefore, using the mean difference between pre- and post-adaptation of 0.19 with a standard deviation of 0.18, we would need a minimum of 9 participants to be able to reject the null hypothesis with a probability (power) of 0.8, presuming *α* < 0.05 (PS Power and Sample Size Calculations, version 3.1.2). Presuming a 25% attrition, we will recruit at least 12 participants for each of the IVE-VPT and VPT-IVE patient cohorts (aims). We aim to enrol 24 service members at the FBCH site and 24 civilians at the JHU Outpatient Center for each of aims I–III.

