**Fig. 2 Fig2:**
[figure not shown]
Algorithm of aim I comparing IVE with VPT, considering 6-week washout and crossover design. Both groups get gait/balance exercises from the beginning. CPG, clinical practice guidelines [17]

For aims II and III, we will also randomize participants initially to the IVE or VPT group with a washout period and crossover to the other intervention. As with aim I, each group from aim II and aim III will participate in rehabilitation at home and will visit the clinic once per week for the modification of the gaze stability exercises. However, participants in aims II and III will have a shortened participation and washout. The duration for participation in aims II and III is reduced from aim I based on our desire to determine ideal dosing for gaze stability training considering burden and compliance. Additionally, the expectation for most patients undergoing vestibular rehabilitation is that 6 weeks is a typical time to expect change (per currently clinical practice guidelines (CPG)) [17].

In aim II, neither IVE nor VPT groups will complete their balance and gait exercises until the washout period begins (Fig. 3). Each group will perform daily gaze stability exercises: VPT control group will follow the recommended CPG (15 min), and members in the IVE group will use the IVE device (15 min). Participants will perform the gaze stability exercises only for 3 weeks, before entering the washout stage for 3 weeks and not perform any explicit rehabilitation. Once they enter washout, they will begin gait/balance home exercises. Once the washout is complete, they will cross over into the other group for gaze stability training and continue with gait/balance exercise and progression (Fig. 3).

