## Statistical methods

### Statistical methods for primary and secondary outcomes {20a}

The primary outcome for determining treatment efficacy is VOR gain, which is measured weekly for each subject in each intervention period. To verify randomization between sequences, baseline demographics and characteristics of vestibular injury will be compared across arms. The primary analysis will follow the intent to treat principle, where patient outcomes are analyzed following how they were randomized and not adjusted or excluded based on adherence to assigned treatment. To determine the efficacy for the primary outcome, a generalized linear mixed model will be used with VOR gain as the dependent factor [31]. This model will be used to compare VOR gain between interventions and to estimate period and carryover effects. With substantial washout periods for each aim, we do not expect there to be substantial differences in the carryover effects between intervention sequences. We will verify there are no differences in the carryover effects by testing for an interaction between treatment and time. If this interaction is statistically significant at *α =* 0.05, we will focus our analysis on patient outcomes in the first period, and disregard outcomes in the following period. We will adjust this model for site as well as demographic and vestibular injury-related factors that are imbalanced between arms at baseline. All statistical tests will be conducted as two-sided for an *α* of 0.05.

For secondary analyses, we will examine the compensatory saccade metrics, which are also measured at each weekly visit similarly to VOR gain. Similar to our analysis of the primary outcome, we will examine this secondary outcome with a generalized linear mixed model, estimating carryover effects by testing for an interaction between period and intervention. We will also adjust these comparisons of VOR gain and compensatory saccade metrics for site and for factors that are imbalanced at baseline. Analyses with greater than 25% loss to follow-up or incompleteness for other reasons will use multiple imputation [31]. All analyses will be conducted using the SAS software version 9.4 (SAS Institute Inc., Cary, NC, USA).

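### The 9-participant, 80% power statement is for a pre-post change on IVE alone in healthy adults, so power for the trial's IVE-versus-VPT comparison is not established

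*Protocol article*

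**What the plan says.** The protocol article's Sample size {14} section names its source: "We have based our estimate of sample size on data published in healthy adults (21–58 years old) using the IVE paradigm". The data are that "active VOR gain pre-adaptation was 0.92 ± 0.18 and active VOR gain post adaptation was 1.11 ± 0.22". From them it concludes, "using the mean difference between pre- and post-adaptation of 0.19 with a standard deviation of 0.18", that "we would need a minimum of 9 participants to be able to reject the null hypothesis with a probability (power) of 0.8". It does not name the null hypothesis. It allows for 25% attrition, raises 9 to 12 for each sequence (IVE-VPT and VPT-IVE), and plans 24 participants at each of two sites for each of aims I to III. It also says that the ages in the source match those of the target patients.

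Statistical methods {20a} sets out the primary analysis, a mixed model for VOR gain: "This model will be used to compare VOR gain between interventions and to estimate period and carryover effects". If the carryover test is significant, the analysis turns to the first period alone. On sidedness it says "All statistical tests will be conducted as two-sided for an" α of 0.05.

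Trial design {8} makes VPT an active standard-of-care arm. Outcomes {12} measures the primary outcome by video head impulse test. Eligibility criteria {10} admits ages 18 to 83, with mild traumatic brain injury or vestibular hypofunction.

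**The concern.** The power statement and the primary analysis answer different questions. The first asks whether gain rises after IVE in healthy people. The second asks whether IVE raises gain more than VPT does in patients. The protocol gives no expected IVE-minus-VPT difference, no SD for it and no power for it.

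The SD is also in doubt on its own terms. A paired calculation needs the SD of the change. The value used, 0.18, is the same as the printed pre-adaptation SD, and the protocol does not say that it is the SD of the change.

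The power statement decides how a null result is read. If IVE and VPT do not differ significantly in one of the three aims, a reader would take that as coming from a test with 80% power. As written, that power belongs to no comparison between randomised treatments.

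**Working it through.** **Inputs from the protocol.** Difference 0.19; SD 0.18; pre and post SDs 0.18 and 0.22; power 0.80; two-sided α 0.05; attrition 25%; 48 enrolled per aim; 1:1 allocation to sequence.

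**Step 1: reproduce the 9.** For a paired (one-sample) t-test, n = ((t₀.₉₇₅ + t₀.₈₀) × SD / difference)², with n − 1 degrees of freedom, solved by iteration.
- At the solution, (2.300 + 0.888) × 0.18 / 0.19 = 3.02, and its square is 9.12.
- Exact noncentral-t power is 0.792 at n = 9 and 0.843 at n = 10.
- Two independent groups with the same inputs need 16 per arm by t-test (15 by normal approximation).
- Attrition: 9 / 0.75 = 12, as stated.

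So the 9 is a paired pre-post calculation on one treatment.

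**Step 2: when would the 9 apply to IVE versus VPT?** The IVE-minus-VPT difference would have to be 0.19. If patients on IVE gained what the healthy adults gained, VPT would have to produce no gain change at all. The SD of the within-participant treatment difference would also have to be about 0.18.

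**Step 3: is 0.18 the SD of the change?** SD of change = √(0.18² + 0.22² − 2r × 0.18 × 0.22), where r is the pre-post correlation. Setting this to 0.18 gives r = 0.22² / (2 × 0.18 × 0.22) = 0.0484 / 0.0792 = 0.61. No correlation is stated. Other values of r give, for the same pre-post test:

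| r | SD of change | n for 80% power | Power at n = 9 |
|---|---|---|---|
| 0.5 | 0.203 | 12 | 0.69 |
| 0 | 0.284 | 20 | 0.42 |

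**Step 4: what the planned enrolment can detect.** Completers per aim: 0.75 × 48 = 36. Using one treatment difference per participant, adjusted for period, with 36 − 2 = 34 degrees of freedom, the detectable difference is about (2.032 + 0.852) × SD / √36 = 0.4807 × SD.

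The protocol gives no SD for the treatment difference, so three are assumed: 0.18 (its own value reused), 0.255 (0.18 × √2, two uncorrelated measurements) and 0.28 (about √(0.18² + 0.22²), the printed SDs uncorrelated). The last column shows power if the true difference were half of 0.19, chosen only for illustration.

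| Assumed SD | Difference detectable with 80% power | Power for 0.095 |
|---|---|---|
| 0.18 | 0.087 | 0.87 |
| 0.255 | 0.123 | 0.58 |
| 0.28 | 0.135 | 0.51 |

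For a difference of the full 0.19, power is above 0.97 at all three SDs.

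**Step 5: first-period fallback.** With 18 completers per arm, the detectable difference is about 2.884 × SD × √(2/18) = 0.961 × SD. That is 0.173 at SD 0.18 and 0.211 at SD 0.22, close to the whole single-arm IVE change of 0.19.

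**The case against.** A reader might infer that the design lacks the 80% power claimed. The documents do not support that. Showing a shortfall needs a true IVE-minus-VPT difference and its SD, and neither is given. No stated comparison rests on 9 completers in total: 9 is raised to 12 per sequence and then to 24 per site and 48 per aim. With 36 completers, power for half of 0.19 is 0.87 at SD 0.18 and about 0.5 at SD 0.28, so the answer depends on the assumption. This part of the objection stands, and it limits the point to power not being established.

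Four further objections have some force.
- That the IVE-versus-VPT difference is smaller than 0.19 is an inference. Outcomes {12} says that VPT improves dizziness and balance-confidence scores, but nowhere does the article say that it raises VOR gain.
- The 0.18 may be a reported SD of change that happens to equal the pre-adaptation SD, and a correlation of 0.61 is not implausible. The article does not settle this.
- VOR gain is measured weekly and will be analysed in a mixed model, so detectable differences from one value per participant are approximate.
- A reader might add that aims II and III, at 3 weeks, rest on no effect estimate, because "6 weeks is a typical time to expect change". The article does not tie the 0.19 to any training duration, so it shows neither a fit nor a misfit at 3 weeks.

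None of this makes the stated 80% apply to the comparison that the trial tests. Nor is this detail that an article leaves to a fuller document: the section states a power and its inputs, and they belong to a different test.

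**Conclusion.** The point holds in this form: the stated power is for a single-arm pre-post change in healthy adults, and power for IVE versus VPT in patients is not established. The mismatch needs no assumption, since the protocol's figure reproduces only as the paired test.

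The size of the consequence does rest on assumptions. With about 36 completers per aim, the trial has 80% power for differences of about 0.087 to 0.135 if the SD of the treatment difference lies between 0.18 and 0.28. In the first-period fallback the range is about 0.17 to 0.21 for SDs of 0.18 to 0.22. Whether those differences are plausible for IVE over VPT cannot be judged from the article.

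The remark on age is a separate, smaller misstatement: the source covers ages 21 to 58 and eligibility runs from 18 to 83. No effect on power is computed from it.

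**What to change.** Keep the enrolment and rewrite the Sample size section.
1. Delete the claim that 9 participants give 80% power.
2. State the IVE-minus-VPT difference detectable with 80% power at 48 per aim (about 36 completers): about 0.087, 0.123 and 0.135 at SDs of 0.18, 0.255 and 0.28, with the SDs labelled as assumptions.
3. Add the first-period fallback (18 per arm): about 0.17 to 0.21 at SDs of 0.18 to 0.22.
4. Say that 0.19 is a single-arm change in active VOR gain in healthy adults using IVE.
5. Remove the remark that the source's ages match the target patients.
6. Give per-site figures only if a within-site analysis is planned; the article describes one model adjusted for site.

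The cost is the rewording of one section, with no extra participants and no change to the analysis. The downside is that the stated figure becomes less favourable than the present claim.

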### Recruitment {15}

Participants will be recruited via a combination of methods that include a chart review, in-person recruitment during clinic visits, and queries garnered using flyers posted in clinics.

### Recruitment at the FBCH

In 2017, 226 SM with mTBI were evaluated for mTBI at FBCH. In the past, researchers from FBCH have had success recruiting 2–3 SM/month with mTBI for participation in studies (personal communication, [name] PT). We intend to screen ~ 10 patients per month for the INVENT VPT, with the intention of enrolling 2–3 participants per month.

### Recruitment at Johns Hopkins University School of Medicine (JHU)

At the JHU Outpatient Center, the principal investigator (PI) of the INVENT VPT routinely sees approximately 20 patients per month with dizziness and balance disorders, ~ 120/year. Of those 20 patients per month, roughly 20% have a peripheral vestibular hypofunction. Therefore, we intend to screen a minimum of 16 patients per month to obtain the required number of enrolled participants with vestibular hypofunction, over the duration of the study.

## Assignment of interventions: allocation

### Sequence generation {16a}

Random assignments to VPT-IVE or IVE-VPT will be allocated on a 1:1 ratio via a computer-generated randomization schedule stratified by the clinical center and utilizing random permuted blocks of random sizes. Block sizes are not disclosed.

### Concealment mechanism {16b}

Participants will be assigned to VPT-IVE or IVE-VPT via an online central randomization program in REDCap that is maintained by the Data Coordinating Center. The random assignment is released to the study coordinator within the REDCap randomization program after the baseline study visit has been completed and the participant has been confirmed as eligible for the trial. The random assignments for the INVENT VPT will be maintained by the Data Coordinating Center and will not be accessible to the study investigators and clinical center personnel.

### Implementation {16c}

Patients who provide informed consent and are deemed eligible for the INVENT VPT Trial will be randomized to IVE-VPT or VPT-IVE. The allocation sequence will be generated by the Data Coordinating Center. Study coordinators will enroll participants after confirming eligibility via a screening form. The coordinator will enter specific baseline assessment data into a computerized randomization program generated in REDCap, and the assignment will be provided after these data are entered and confirmed by the study coordinator. The sequence of allocations will not be disclosed to the study site and will be maintained by the Data Coordinating Center.

## Assignment of interventions: blinding

### Who will be blinded {17a}

Due to the nature of the interventions, study participants and the research physical therapists administering the interventions are unable to be blinded/masked to treatment assignment. The study coordinator is unmasked to treatment assignment as they are involved in the randomization process. The research physical therapist will not be involved in the measurement of any trial outcomes. The research audiologist will be masked to treatment assignment and will conduct the auditory and vestibular function tests. A member of the research team other than the research physical therapist/audiologist will conduct the measurement of all trial outcomes. Participants and unmasked research personnel will be advised not to share treatment assignments during the follow-up visits. INVENT VPT study forms that disclose treatment allocation will be entered by the study coordinator, and these study forms will be kept separate from the participant’s medical records.

